## Allocation Concealment

The allocation will be concealed from the investigator who is conducting the enrolment and outcome assessments. The independent researcher who is responsible for the randomisation will not release the randomisation code to the treating physiotherapist electronically until the patient has been recruited into the trial.

## Implementation of sequence allocation

The blinded assessor will be a specialist physiotherapist in neurosurgery who will inform the independent researcher when a new participant has been enrolled, and their baseline measures collected. Once randomised, the independent researcher will provide the outcome of the randomisation to the treatment physiotherapist, who will inform the participant of their group allocation by phone. The treating physiotherapists will not be involved in the outcome assessment and will not inform the blinded assessor of the sequence allocation.

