## Outcomes

Table 1 describes the primary and secondary outcomes and the mediators of change.

**Table 1 Tab1:** Primary and secondary outcomes and mediators of change.

Primary	Secondary	Mediators of change
• Incidence of mild stable DCM in the neurosurgical OPD clinics. • The proportion of people with mild stable DCM who meet the eligibility criteria. • Recruitment rate (per month). • Participant and clinician adherence to the physical rehabilitation intervention. • Acceptability of the intervention to the participants and clinicians. • Burden of measurement tool completion. • Participant retention.	• Physical functioning (Physical component score of the Short Form 36). • Myelopathy severity (mJOA). • Neck pain related disability (Neck disability index). • Neck pain and arm pain severity (numerical rating scale). • Spinal adverse event (spinal adverse events severity scale).	• Cervical Range of motion • Manual dexterity (9 Hole peg test) • Grip strength • Neck Strength • Free living physical activity. • Timed up and go test

*DCM* degenerative cervical myelopathy, *OPD* outpatient department, *mJOA* modified japanese orthopedic association scoring system.

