## Blinding

Every participant will have a unique identifier. Clinicians delivering the interventions and trial participants will not be blinded to group allocations due to the nature of the intervention. Participants will be asked in advance of attending for their 12 week follow up not to disclose their group allocation with the outcome assessor. Data analysts will be blinded to group allocation. Unblinding will only occur in exceptional circumstances when knowledge of the group allocation is essential for further management of the participant.

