### Data collection methods

The process for data collection will be standardised and explicitly described in the trial manual. Training in recording data relevant to the assessment of intervention fidelity and adverse events will be included in the trial workshops for treating physiotherapists.

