## Harms

A risk of a serious adverse event related to the physical rehabilitation intervention is minimal. All adverse events that occur after the participant has been enrolled in the trial until the 12 week follow up will be recorded. The treating physiotherapists will be prompted to enquire about any adverse events at every scheduled appointment with structured questions and recording the outcomes in a standardised data collection sheet. They will also undertake standardised assessments of participants neurological function at every scheduled session and will refer participants to their consulting neurosurgeon if there is any significant neurological deterioration. The investigators will determine the relatedness of an event to trial intervention based on a temporal relationship, as well as whether the event is unexpected or unexplained given the subject’s clinical course, the natural history of DCM and previous medical conditions. The investigators will suspend the trial if more than one serious adverse events of any kind occur, and these are related or caused by the physical rehabilitation intervention from the trial. If the cause of the events cannot be identified or addressed or is plausibly related to the intervention, the trial will be terminated.

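### Spinal adverse events are a secondary outcome, yet the only collection route described is recording by unblinded treating physiotherapists, whom the protocol excludes from outcome assessment

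*Protocol article*

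**What the plan says.** Four parts of the protocol article bear on this point.

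- **Implementation of sequence allocation.** A specialist physiotherapist acts as blinded assessor. Of the treatment staff it says: "The treating physiotherapists will not be involved in the outcome assessment". No outcome is excepted.
- **Outcomes, Table 1.** The secondary column has five lines: SF-36 physical component score, mJOA, Neck Disability Index, neck and arm pain ratings, and "Spinal adverse event (spinal adverse events severity scale").
- **Harms and Data collection methods.** Events are to be captured from enrolment to the 12-week follow-up. The route described is: "The treating physiotherapists will be prompted to enquire about any adverse events at every scheduled appointment with structured questions and recording the outcomes" on a standardised sheet. Training matches this role: "Training in recording data relevant to the assessment of intervention fidelity and adverse events will be included in the trial workshops for treating physiotherapists". The investigators judge whether an event is related to the intervention.
- **Blinding.** "Clinicians delivering the interventions and trial participants will not be blinded to group allocations due to the nature of the intervention".

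The article does not state who applies the severity scale. It refers measurement detail for all secondary outcomes to Appendix A.

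**The concern.** Read together, the allocation and blinding sections tell the reader that outcomes are assessed by someone who does not know the arm and that treatment staff stay out of it. For spinal adverse events, the only route described runs through treatment staff who do know the arm.

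Deciding whether a symptom is worth recording as an event takes judgement. A recorder who delivers the intervention may, without intending to, record more or fewer events in one arm. The Introduction names safety as something to be explored before a definitive trial can be designed, and this is the only safety line in Table 1. A description of events by arm that is taken to be assessor-blind when it is not could mislead the design of that later trial.

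**Working it through.** The check is a comparison of statements. The plan gives no figure to reproduce.

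**Step 1: Is it an outcome or only monitoring?** Table 1 places spinal adverse events in the secondary outcome column, with a named scale. It is an outcome.

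**Step 2: Who collects it?** The Harms section and the training sentence in Data collection methods both name the treating physiotherapists. The article names no other person as asking about or recording adverse events.

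**Step 3: Do they know the arm?** Yes. The Blinding section says so, and under Implementation of sequence allocation it is the treating physiotherapist who tells the participant the allocation.

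**Step 4: Is there an exception to the exclusion sentence?** No. It is unqualified.

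**Step 5: Put together.**

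| Statement | Applied to spinal adverse events |
|---|---|
| Treating physiotherapists take no part in outcome assessment | They ask about and record the events |
| Outcome assessor is blinded | The only named recorders are unblinded |
| Severity scale is the measure | Grader not named in the article |

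The first two rows conflict for elicitation and recording. The third is open, not contradictory.

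**Step 6: Is there a common ascertainment point?** The Harms route depends on scheduled appointments. The eligibility criteria describe up to 10 supervised sessions in the rehabilitation arm. The Clinical surveillance section describes a single education session, then follow-up at 12 weeks. The article does not say whether events are asked about at the education session. The 12-week visit is the scheduled contact that both arms share, and the blinded assessor attends it.

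**Step 7: Scale.** Inputs: 24 participants planned, 12 per arm (Sample size). If one participant is counted as having an event, or not, because of who recorded it, that arm's proportion moves by 1/12 = 0.083, or 8.3 percentage points. This assumes exactly 12 in the arm, which simple randomisation does not guarantee. The same step size applies to any yes/no outcome in an arm of this size. It shows how coarse the outcome is and does not estimate bias. The documents give no event rate or misclassification probability from which bias could be estimated.

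**The case against.** The strongest case on the other side has five parts.

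1. **Scope of the sentence.** It sits beside the description of the blinded assessor and the baseline measures, and may have been meant only for the assessor's own visits. That is plausible, but the sentence does not say so. If it was the intent, a clarifying clause is still needed.

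2. **The assessor may already complete the scale at 12 weeks.** The Abstract says that secondary outcomes are completed at baseline and 12 weeks, and the Harms section never mentions the scale. The article does not exclude this reading. Nor does it state it, and the only enquiry about events that it describes is by the physiotherapists.

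3. **Grading.** A reader might infer that the physiotherapists also grade severity and could grade events down. The documents do not support that. They show asking and recording only; relatedness is for the investigators, and the grader may be named in Appendix A. The point is therefore limited to elicitation and recording. Blinded grading elsewhere would not fully cure it, since an event that is never recorded cannot be graded.

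4. **Ordinary practice.** Treating clinicians commonly record harms. This stands, and nothing here argues for stopping it. The conflict arises because the events are also a named outcome.

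5. **Participants are unblinded.** An event told to a blinded assessor is still an unblinded participant's report, as with the self-reported outcomes in Table 1. This also stands: the change would make ascertainment assessor-blind and common to both arms, not fully blind.

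**Conclusion.** The inconsistency is real and limited. The article excludes treating physiotherapists from outcome assessment without qualification, yet for one of five secondary outcome lines, the only one on safety, they are the only people it names as asking about and recording events, and they know the arm. The separation does not hold for elicitation and recording of that outcome.

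The conclusion rests on the visible text. If Appendix A gives the 12-week enquiry to the blinded assessor, what remains is a wording correction. No direction or amount of bias can be derived from the documents, and a reader should not infer that bias has been shown. No primary feasibility metric or sample size figure changes. The trial suspension provision rests on the investigators' judgement of related serious events and is not affected. The matter deserves correction because a cheap improvement is available; it does not threaten the trial.

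**What to change.** - Keep the physiotherapists' per-session enquiry and recording as it is, for safety monitoring.
- Add a scripted adverse-event enquiry by the existing blinded assessor at the 12-week visit. Use identical wording in both arms, ask it after all other measures, and include no questions about sessions or exercises. Make this the source for the between-arm description of the Table 1 outcome, and state who grades the severity scale.
- Report physiotherapist-recorded events separately, labelled as collected unblinded.
- Amend the sentence under Implementation of sequence allocation to say that treating physiotherapists record adverse events for safety monitoring and are otherwise not involved in outcome assessment.

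**Cost.** A short addition to a visit already planned, with existing staff, plus the wording change.

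**Downsides.** The assessor's enquiry relies on recall over up to 12 weeks; keeping the per-session records offsets this. A participant's account may reveal the arm, but only once every other measure is complete. Participants' reports remain unblinded, and the report should say so.

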## Blinding

Every participant will have a unique identifier. Clinicians delivering the interventions and trial participants will not be blinded to group allocations due to the nature of the intervention. Participants will be asked in advance of attending for their 12 week follow up not to disclose their group allocation with the outcome assessor. Data analysts will be blinded to group allocation. Unblinding will only occur in exceptional circumstances when knowledge of the group allocation is essential for further management of the participant.

### Data collection methods

The process for data collection will be standardised and explicitly described in the trial manual. Training in recording data relevant to the assessment of intervention fidelity and adverse events will be included in the trial workshops for treating physiotherapists.

### Data management

A trial code book will be generated for raw, non-numeric data and a standard process will be developed and implemented to improve the accuracy of data entry and coding in the trial database which will be explicitly described in the trial handbook. The data will be periodically checked for errors and the source documentation will be used to verify the data accuracy as required.

### Statistical analysis

Statistical analysis will be performed using STATA (Version 19) software.

The data will be checked for normality, then appropriate descriptive analyses will be used to summarise participant characteristics and outcomes. Feasibility, the primary outcome of this study, will be evaluated by calculating the following recruitment, adherence, and retention metrics:Incident rate of mild DCM in new referrals to the neurosurgical outpatient clinic (reported per month of recruitment period).The proportion of people with mild DCM who were eligible for enrolment.The proportion of eligible people who consented to participate.The proportion of participants who attended their 12 week follow up in both intervention groups.The proportion of participants who attended their scheduled physiotherapy sessions in the physical rehabilitation group.The number of core intervention components included in each treatment session.

The quantitative process data will be analysed before trial outcomes to avoid bias interpretation[13]. Intervention effects will be represented by point estimates and their standard deviations. Confidence intervals will be calculated and will be interpreted with regards to the minimum clinically important difference. This data will be used to estimate a sample size required for a definitive trial, if appropriate [12].

Semi-structured interviews of the participants and clinicians will be audio recorded, transcribed verbatim and analysed thematically. The interviews will map to the theoretical framework of acceptability [14]. Findings will be reported according to the COREQ guidelines for qualitative research.

A traffic light system of green (go), amber (amend) and red (stop) which will specify the recruitment, adherence, retention, and signal of efficacy criteria for progression to a main trail will be specified a priori.

## Harms

A risk of a serious adverse event related to the physical rehabilitation intervention is minimal. All adverse events that occur after the participant has been enrolled in the trial until the 12 week follow up will be recorded. The treating physiotherapists will be prompted to enquire about any adverse events at every scheduled appointment with structured questions and recording the outcomes in a standardised data collection sheet. They will also undertake standardised assessments of participants neurological function at every scheduled session and will refer participants to their consulting neurosurgeon if there is any significant neurological deterioration. The investigators will determine the relatedness of an event to trial intervention based on a temporal relationship, as well as whether the event is unexpected or unexplained given the subject’s clinical course, the natural history of DCM and previous medical conditions. The investigators will suspend the trial if more than one serious adverse events of any kind occur, and these are related or caused by the physical rehabilitation intervention from the trial. If the cause of the events cannot be identified or addressed or is plausibly related to the intervention, the trial will be terminated.

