**The exclusion criteria are:**
Patient or surgeon preference for urgent surgical decompression for progressive DCM, motor radiculopathy or severe unrelenting radicular arm pain or significant risk factors for progression including co-existing cervical radiculopathy and circumferential cord compression.Diagnosis of other neurological condition that could confound assessment.Involvement in another clinical study or trial.Pregnancy.If the participant is unable to commit to a 12-week programme of up to 10 sessions of supervised physical rehabilitation and participating in a regular home exercise programme for the duration of the study.

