## Clinical surveillance

Participants assigned to the clinical surveillance control group will be invited to attend a single, one to one education session which will be supplemented with a written patient information booklet after which they will be scheduled for a 12 week follow up.

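### Structured adverse event questions and neurological checks follow treatment sessions, so a between-arm summary that pools session-elicited events would tend to overstate minor and transient events in the rehabilitation arm

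*Protocol article*

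**What the plan says.** The Harms section sets one recording window for everyone: "All adverse events that occur after the participant has been enrolled in the trial until the 12 week follow up will be recorded". It then describes who asks and when: "The treating physiotherapists will be prompted to enquire about any adverse events at every scheduled appointment with structured questions". The same staff examine participants: "They will also undertake standardised assessments of participants neurological function at every scheduled session".

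The number of such occasions differs by arm. Under the exclusion criteria a candidate is ineligible if "unable to commit to a 12-week programme of up to 10 sessions of supervised physical rehabilitation", so rehabilitation means up to 10 sessions. Control participants "will be invited to attend a single, one to one education session", "after which they will be scheduled for a 12 week follow up". The Clinical surveillance section does not say who gives that session or exactly when.

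Training in adverse event recording is mentioned only for the same staff: "adverse events will be included in the trial workshops for treating physiotherapists". Under the sequence implementation section, they have no part in the outcome assessment.

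Harms are a listed outcome. The secondary column of Table 1 includes "Spinal adverse event (spinal adverse events severity scale"). The Introduction names safety among the things to be explored before a definitive trial.

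Both arms have two other channels, described under Interventions: instructions to contact the surgical team about neurological deterioration, and a logbook of contacts with other healthcare providers for neck and upper limb symptoms.

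**The concern.** Active ascertainment is tied to treatment exposure. A participant who is asked structured questions and examined up to 10 times will report more short-lived complaints, and show more passing neurological changes, than one who is asked once and next seen at week 12. This holds even if the two have the same true experience.

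If all these records go into one table by arm, the rehabilitation column is inflated by the way the data were gathered. With 12 participants planned per arm, a handful of minor session-elicited complaints could dominate such a table. The safety picture carried to a definitive trial would then reflect the questioning schedule as well as the intervention.

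**Working it through.** The article states no harms rate and no harms comparison, so there is no figure to reproduce. The check has two parts.

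**1. Contact counts, from the document.** Active enquiries by treating physiotherapists number up to 10 under rehabilitation and at most 1 under control. The control figure is inferred, because the person giving the education session is not named. If the common 12-week visit also asks, the counts become up to 11 against 2.

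**2. Direction and possible size, by illustration.** The assumptions below are not in the document:
- The true event rate is the same in both arms, and events are spread evenly over 12 weeks.
- Rehabilitation sessions are evenly spaced from week 0.5 to week 11.5, and the control session is at week 0.5.
- An event is reported at the next enquiry with probability 0.5^(delay/h), where h is a recall half-life in weeks.

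For enquiries separated by gaps g, the proportion of events captured is

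(1/12) × Σ (h/ln 2) × (1 − 2^(−g/h)).

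Worked case: h = 4, week 12 also asks, so h/ln 2 = 5.771.
- Control has gaps of 0.5 and 11.5 weeks: 5.771 × (0.083 + 0.864)/12 = 0.46.
- Rehabilitation with 10 sessions has nine gaps of 11/9 = 1.222 weeks and two of 0.5: 5.771 × (9 × 0.191 + 2 × 0.083)/12 = 0.91.
- The ratio is 1.99, about 2.0.

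All cases with a week-12 enquiry in both arms:

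| Recall half-life | Rehabilitation, 10 sessions | Control | Ratio, 10 sessions | Ratio, 6 sessions |
|---|---|---|---|---|
| 2 weeks | 82% | 27% | 3.0 | 2.6 |
| 4 weeks | 91% | 46% | 2.0 | 1.9 |
| 8 weeks | 95% | 65% | 1.5 | 1.4 |
| Complete recall | 100% | 100% | 1.0 | 1.0 |

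If week 12 does not ask, active enquiry captures about 4% of events in control (the half week before its one session) against 79% to 96% with 10 rehabilitation sessions. That case leaves out self-referral and the logbook, so it is an extreme and not an expectation.

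If both arms were asked on the same schedule, the expected ratio would be 1.0 for any half-life.

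**The case against.** The strongest reply is that the article is a condensed account. Appendix A gives time points for every secondary outcome and is not shown. The Abstract places the secondary outcomes at baseline and 12 weeks, and both arms attend the 12-week visit. A reader might infer from the Harms section that controls are never asked about adverse events after their education session. The documents do not support that, since a week-12 enquiry may well be specified elsewhere. Even so, such an enquiry would narrow the asymmetry without removing it, because the session enquiries described in the article would still add events in one arm only.

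A second reply is that no between-arm harms contrast is planned. The Statistical analysis section describes summaries, and it reads effect estimates against minimum clinically important differences, which do not suit event counts. The progression criteria it names are recruitment, adherence, retention and signal of efficacy. The suspension rule counts only serious events related to or caused by rehabilitation. All of this stands. The concern therefore applies only to a summary by arm that pools the sources; no decision rule is undermined.

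A third reply is that both arms can self-refer and both keep a logbook. These help, but the first is unsolicited and the second records healthcare contacts rather than adverse events. Neither matches repeated structured questioning.

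Finally, close monitoring of the exposed arm serves the aim of exploring the intervention's safety. That is so, and nothing here argues against it.

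**Conclusion.** The point holds as a matter of ascertainment and reporting. Followed as written, the plan will tend to record more minor and transient events under rehabilitation at equal true rates, and a pooled summary by arm would carry that forward. The direction needs only that enquiry is more frequent in one arm and that recall is incomplete.

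The size is not known. The ratios of 1.4 to 3.0 rest wholly on the assumed recall half-lives and session spacing, and the ratio falls to 1.0 with complete recall at a common week-12 enquiry. A reader might take them as an estimate of bias in this trial; the document gives no basis for that.

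A reader might also infer that the comparison of deterioration in general is compromised. It is not. Lasting deterioration is measured by the mJOA in both arms at 12 weeks, and serious events are much less dependent on prompting. The primary feasibility outcomes are untouched. The change is worth making because it is cheap and protects a named secondary outcome.

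**What to change.** State that any between-arm adverse event summary will use only information gathered identically in both arms:
- the same structured form, completed by the participant at the existing 12-week visit, so that the blinded assessor does not learn the allocation from the answers; and
- an adverse event page added to the logbook that both arms already keep.

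If Appendix A already specifies a common week-12 enquiry, the change reduces to the logbook page, participant completion and the reporting rule.

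Leave session monitoring unchanged. Report session-elicited events and session neurological findings separately for the rehabilitation arm, as safety data under exposure, with no between-arm contrast.

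The cost is one form and one logbook page, with no extra visits or staff. The drawback is that the comparative count will miss some transient events found only at sessions, though these are still reported separately. Some bias may also remain, because participants questioned repeatedly during treatment may recall more at week 12.
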